##### Study instruments

Research question 1: does using the IBH-PC toolkit, a practice-level intervention, affect patient-centered outcomes in adults with multiple chronic medical and behavioral health conditions?

Our primary outcome, the PROMIS-29 [35], is a set of person-centered measures of physical, mental, emotional, and social health included in the National Institute of Health’s (NIH) measurement toolbox. Rather than a disease-focused measurement system, it provides valid measures of Physical Function, Anxiety, Depression, Fatigue, Sleep Disturbance, Social Functioning, and Pain. These aspects of functioning and well-being are relevant across many chronic conditions and broadly represent “health-related quality of life.”

Additional instruments will be used to collect secondary outcomes:
The Consultation and Relational Empathy [36] (CARE) survey is a 10-item validated self-report measure that assesses patients’ perception of provider empathy. The CARE has been shown to have excellent reliability (Cronbach’s alpha 0.92).The Modified Self-reported Medication-taking Scale [37] is the Morisky Green Levine Scale (MGLS) four-item self-report measure assessing adherence to prescription medication. The MGLS has been shown to have adequate reliability (Cronbach alpha = 0.61 [56]).The Utilization Patient Report [38] is a 3-item self-report measure asking patients to recall their healthcare utilization in the past year. Specifically, patients are asked to report utilization of visits to the emergency room, overnights in the hospital, and outpatient appointments to a healthcare provider.Time loss due to disability will be measured using the Restricted Activity Days survey [57]. This survey asks patients to report on the restriction of their daily lives due to illness and disability.Physical function will be measured using the Duke Activity Status Index [40] (DASI), a 12-item validated self-report measurement used to assess functional capacity. The DASI has been shown to have good to excellent reliability in several studies (Cronbach’s alpha ranging from 0.80 to 0.93 [58]) and correlates with peak oxygen uptake measured by exercise stress test.Patient-centered primary care will be measured using the Patient Centered Index (PCI), a 16-item questionnaire. This tool was developed for use in the IBH-PC study by a team of researchers, patients, and other stakeholders to assess how a patient perceives their care. Reliability and validation measures are not yet available.The 7-item Generalized Anxiety Disorder Scale [42] (GAD-7) is a self-report questionnaire developed and validated in a larger primary care patient sample to assess anxiety symptom severity. The GAD-7 has been shown to have excellent reliability in several studies (Cronbach’s alpha ranging from 0.79 to 0.91 [59]).The 9-item Patient Health Questionnaire [41] (PHQ-9) is a validated self-report measure of depression symptom severity. The PHQ-9 has shown to have good reliability (Cronbach’s alpha ranging from 0.86 to 0.89 [41]). Recognizing the sensitive nature of the questions on the PHQ-9 concerning suicidal thoughts and ideation, information on how to access the national suicide helpline was distributed with all paper study materials and was programmed into the electronic survey data capture system.The Asthma Symptom Utility Index [43, 44] (ASUI) is a 10-item validated self-report measure assessing control and quality of life as it relates to asthma symptoms. Reliability for the ASUI is considered good with a Cronbach’s alpha of 0.74 [43].Alcohol use will be assessed using 2-items from the Self-Report Habit Index-Alcohol [46] (SRHI-A). The SRHI-A has shown to have excellent reliability (Cronbach’s alpha 0.94 [46]).Substance Use Disorder will be assessed using the 5-item Substance Disorders subscale of the Global Assessment of Individual Needs-Short Screener [45] (GAIN-SS), a biopsychosocial screener for individuals presenting with substance use and mental health concerns. The GAIN-SS Substance Use subscale has been shown to have acceptable reliability (Cronbach’s alpha ranging from 0.77 to 0.84 [60]).

Research question 2: does using the IBH-PC toolkit affect the degree of practice-level behavioral health care integration in primary care practices?

The Practice Integration Profile (PIP) is a survey of 30 items completed by primary care providers and staff about their own practice [26, 27]. It provides a total integration score and 6 domain scores: practice workflow, clinical services, integration methods, case identification, patient engagement, and workspace arrangement and infrastructure.

Research question 3: what factors support or impede successful integration of behavioral health care into primary care practices?

A cross-case comparative analysis [53, 61, 62] will be conducted in selected practices. Researchers will collect data contained in field notes, such as observations of the physical layout of the practice, workflow, and practice meetings; transcripts of semi-structured interviews with coaches, cluster leaders, and practice staff; and relevant site documents.

Research question 4: what are the costs of implementing the IBH-PC toolkit?

A dedicated staff member from each of selected active study sites will periodically complete an in-depth program implementation Cost Assessment Tool (CAT). The CAT is a role-based time-effort evaluation instrument listing the number and type of practice staff participating in each toolkit activity. We will total the time various practice members engage with each component of the IBH-PC toolkit over a 24-month period and calculate the time-effort and cost in US dollars using median total compensation rates appropriate for the practice’s ZIP code and the practice staff’s professional roles. We will also include any supply, equipment, capital, or other non-personnel costs, including training time and coaching time associated with toolkit implementation. Time-effort data collected from participating practices by each participant and subtask will be analyzed for completeness, range and “face validity” of time estimates, and appropriateness of data to determine econometric outcomes. Key variables will then be estimated from global and sub-group averages, including total time and corresponding cost of program implementation steps, time/cost of the planning phase, and those of all implementation phases.

#### Plans to promote participant retention and complete follow-up {18b}

First, each practice receives financial support for a clinical leader and a practice manager to attend to data collection and other non-clinical (research-related) aspects of the project. Second, practice sites are organized into clusters of about 5–7 practices. Each cluster has a designated local Cluster PI (a behavioral or medical provider or researcher). The Cluster PI serves as a member of the research team and coordinates research activities, engages upper practice management, and provides liaison with the investigators. Third, all control practices have access to the intervention (the IBH-PC toolkit) upon completion of the follow-up assessments.

To encourage patient participants to remain engaged and complete the baseline and follow-up surveys, we include a midpoint survey data collection time point to minimize the time in between research contacts and pay patient participants $30 upon completion of each survey ($90 total).

### Data management {19}

The research team developed a written data governance policy to guide appropriate storage and use of study data. Data from consented patient participants are collected electronically, on paper, and over the phone. To complete baseline, midpoint, and follow-up patient surveys, the study team contacts patient participants by each of these three methods over a 3-month period until a response is received or the 3-month window is reached. The following steps are taken:
All patient participants with email addresses are emailed at week zero.Three email reminders are sent every other day if there is no response.At week one, a paper survey is sent to the patient participant’s mailing address.At week five, a second batch of emails is sent followed by two phone calls 1 week later. If the patient participant cannot be reached via phone, a voicemail is left.At week eight, a second paper mailer is sent to patient participants who have yet to respond.At weeks nine through twelve, two more emails and two more phone calls are attempted before concluding efforts.

Data collected electronically via REDCap are automatically captured and stored in REDCap. Trained research assistants sort and enter paper surveys into REDCap and then they are filed and stored in a locked filing cabinet inside a locked office. Postal address, email, and phone number are verified for accuracy and updated as need. Phone surveys are conducted by trained research assistants and information is entered directly into REDCap. Patient participants who submitted surveys with missing data are contacted by telephone to complete the survey. Double data entry is performed, by a team of trained research assistants, on a randomly selected subset of 10% of the surveys received for each time point (baseline, midpoint, and follow-up). If the data entry error rate is greater than 0.05%, the entire batch of surveys is re-entered.

### Confidentiality {27}

Data from EMRs used to recruit patient subjects are extracted, transformed, loaded and curated from clinical practice sites by the DARTNet Institute. DARTNet uses a HIPAA-compliant sFTP cloud transfer system. This includes encryption of all data in transit and deletion of the data as soon as the transfer is complete. Data files transferred to DARTNet are immediately moved behind a second firewall where access is internet protocol address (IP)-to-IP controlled. All file manipulations occur behind this second firewall. Once DARTNet has completed subject recruitment, they use a similar system, Egnyte [63], to transfer the list of patients on a practice’s Community Panel to a practice.

Patient names, medical record numbers, and other unique identifiers are stripped and replaced with a unique study identifier before transferring EMR files to the UVM research team. Electronic medical record files contain data on healthcare visits, clinical measures including blood pressure and hemoglobin A1C, as well as medication and problem lists. Only research personnel authorized to access data for the proposed project have access to the data.

After transfer of EMR data to UVM, all source material, copies, data files, transcripts, and other research materials are maintained in a secure environment with access restricted to members of the study Data and Analysis Team.

Online patient and practice surveys are collected and managed using the REDCap system [55], a secure, web-based application designed to support data capture for research studies.

Physical copies of any patient surveys or other research documents with potentially identifying information are kept under lock and key. Digital materials are secured behind password-protected firewalls.

### Plans for collection, laboratory evaluation, and storage of biological specimens for genetic or molecular analysis in this trial/future use {33}

Not applicable. Biological specimens are not collected as part of this study.

### Statistical methods

#### Statistical methods for primary and secondary outcomes {20a}

Research question 1: does using the IBH-PC toolkit, a practice-level intervention, affect patient-centered outcomes in adults with multiple chronic medical and behavioral health conditions?

For the primary outcomes, we will use generalized linear mixed (GLM) models [64] of patient health status (PROMIS-29 scales) to perform intention-to-treat analyses [65] as a function of experimental condition (active vs. control) and patient characteristics, with patients clustered within practices. The parameters of interest are the central tendency (mean), statistical significance (*P* values), and 95% confidence intervals (CI) of the adjusted change in PROMIS-29 domain from baseline to follow-up. Each of the 8 outcome domains in the PROMIS-29 will be modeled individually as 8 separate hypotheses with adjustment for multiple comparisons and for clustering within practices.

Patient characteristics will be measured at baseline and will include age, gender, race, ethnicity, marital status, employment, education, and income.

For secondary patient outcomes, including change in other patient-reported measures of health and quality of care, and measures of patient disease control from baseline to follow-up, we will use similar GLM models as above but will not adjust for multiple comparisons.

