### Outcomes {12}

#### Research question 1: does using the IBH-PC toolkit, a practice-level intervention, affect patient-centered outcomes in adult patients with multiple chronic medical and behavioral health conditions?

##### Primary outcomes

Change in mean patient Patient-Reported Outcomes Measurement Information System [35] (PROMIS-29) scores from baseline to follow-up for eight domains:
Physical functionAnxietyDepressionFatigueSleep disturbanceSocial functioningPain intensityPain interference

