### Data collection and management

#### Plans for assessment and collection of outcomes {18a}

The main source of outcomes data and descriptors are the patients and practices themselves. On-line surveys are collected and managed using the Research Electronic Data Capture (REDCap) system, a secure, web-based application designed to support data capture for research studies [55]. We also offer patients the option of completing the forms by telephone with a trained interviewer using a scripted interview, or via paper using a mail-in option. Outcome measures are collected at three timepoints: baseline, midpoint, and follow-up. The baseline period reflects the first 0–12 months of participation after randomization, midpoint is 9–12 months after baseline, and follow-up is 18–21 months after baseline. The Data and Analysis Team reviews all records for potential errors.

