### Methods in analysis to handle protocol non-adherence and any statistical methods to handle missing data {20c}

We will employ the “intention-to-treat” principle; analyses will be conducted according to a practice’s randomization assignment. The final analysis population will be fully described and differences from the enrolled population will be presented. An advantage of GLM models with time of measurement as an explicit covariate is that equal numbers of data points and equally spaced intervals between data points are not required [68], so subjects without complete data still contribute to the analysis. Cases that are lost may remain in the analysis, although they will provide less information and reduce the variance of estimated effects less than cases that are present for all measurement times.

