## Trial status

The IBH-PC study information is available on ClinicalTrials.gov, protocol version 4, April 16, 2019. Practice recruitment began when the study was funded on April 1, 2016. Currently, 45 primary care practices have been recruited for study participation. Two of these practices are participating as “Vanguard” (pilot) sites and are not contributing data to the main analyses. One practice withdrew from the study, leaving 42 participating practices. Twenty of these practices are randomized to the active arm and 22 to the control arm.

Patient participant recruitment began in September 2017. Currently, there are 3006 patient participants who have completed baseline surveys and may be eligible for the main analyses if they complete follow-up surveys. Follow-up data collection concluded in December 2020. Data processing is underway.

Eight IBH-PC active practices have been recruited for inclusion in the qualitative case study analysis focused on examining factors associated with supporting or impeding behavioral health integration and data collection is complete. For the cost assessment analysis, 8 IBH-PC active practices were been recruited and data collection is complete. Recruitment and data collection were completed in December 2020.

Due to the complex nature of the study intervention and potential need to respond with modifications, the study team chose to submit the protocol for publication near the conclusion of the follow-up data collection period in order to ensure accuracy in the reported details.

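### The primary PROMIS-29 models list sociodemographic covariates but not the domain's own baseline score, so precision is lost unless an unstated constraint on baseline means applies

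*Protocol article*

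**What the plan says.** The primary outcomes are changes in mean PROMIS-29 "scores from baseline to follow-up for eight domains" (Primary outcomes). Under Statistical methods {20a}, the scales are modelled "as a function of experimental condition (active vs. control) and patient characteristics, with patients clustered within practices", and the parameter of interest is the "adjusted change in PROMIS-29 domain from baseline to follow-up". The covariates are then itemised: "Patient characteristics will be measured at baseline and will include age, gender, race, ethnicity, marital status, employment, education, and income". All eight are sociodemographic.

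The baseline outcome is available: "Outcome measures are collected at three timepoints: baseline, midpoint, and follow-up" (section {18a}). Its timing is also given there: "The baseline period reflects the first 0–12 months of participation after randomization".

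Two other places bear on how baseline enters the analysis. The missing-data section {20c} describes "GLM models with time of measurement as an explicit covariate", in which patients with incomplete data still contribute. Trial status says that the 3006 patients with baseline surveys "may be eligible for the main analyses if they complete follow-up surveys". The first suggests a repeated-measures model; the second leans towards an analysis of completers. Neither says whether the two arms share a common baseline mean.

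**The concern.** A patient's earlier score on the same scale would be expected to predict the later score better than demographic items do, although the documents give no figure for this. An analysis of change uses the baseline only by subtraction, with its coefficient fixed at 1. Estimating the coefficient gives a smaller variance whenever the correlation is below 1.

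Subtraction also overcorrects a chance baseline difference, because part of that difference would have regressed to the mean anyway. Such differences are plausible here: 20 and 22 practices remain, and randomization is stratified on practice integration score and geography, not on PROMIS.

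At stake are wider intervals in up to eight primary comparisons, each tested at 0.00625, when the variable that would narrow them is already in the data set.

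**Working it through.** **Inputs from Sample size {14}:** 40 practices of 75 patients (1500 per arm), SD 10, ICC 0.03, difference 2.5 points, alpha 0.05/8 = 0.00625, stated power 90%. The SD is that of a single score, so the calculation takes no credit for baseline. **Assumed:** the baseline-to-follow-up correlation r, which the article does not give, and the same ICC for both analyses.

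**1. The plan's own figure.**
- Design effect = 1 + 74 × 0.03 = 3.22, so the effective n per arm is 1500/3.22 = 465.8.
- SE = 10 × √(2/465.8) = 0.655.
- Two-sided normal power = Φ(2.5/0.655 − 2.734) = Φ(1.08) = 86.0%. One-sided it is 90.6%.

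The article does not state sidedness, so 90% is reached with a one-sided test. Two-sided power is used below for both analyses. The gap between 86.0% and 90% is a separate matter.

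**2. Change score against baseline-adjusted score.** Relative to the variance of follow-up scores alone, the factors are:
- change: 2(1 − r)
- baseline-adjusted: 1 − r² = (1 − r)(1 + r)
- ratio, adjusted to change: (1 + r)/2

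Each SE is 0.655 times the square root of its factor.

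| r | factor, change | factor, adjusted | ratio | SE, change | SE, adjusted | power, change | power, adjusted | detectable at 90%, change / adjusted |
|---|---|---|---|---|---|---|---|---|
| 0.5 | 1.00 | 0.75 | 0.75 | 0.655 | 0.567 | 86.0% | 95.3% | 2.63 / 2.28 |
| 0.6 | 0.80 | 0.64 | 0.80 | 0.586 | 0.524 | 93.7% | 97.9% | 2.35 / 2.11 |
| 0.7 | 0.60 | 0.51 | 0.85 | 0.508 | 0.468 | 98.6% | 99.6% | 2.04 / 1.88 |
| 0.8 | 0.40 | 0.36 | 0.90 | 0.414 | 0.393 | 99.9% or more | 99.9% or more | 1.66 / 1.58 |

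The SE falls by 13%, 11%, 8% and 5%. Below r = 0.5 the change factor exceeds 1, so change is noisier than the follow-up score alone; the adjusted factor never exceeds 1.

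At 2 points, the lower end of the range of minimally important differences that the article cites for other PROMIS instruments, power for change against adjusted is 62.5% vs 78.5% (r = 0.5), 75.1% vs 86.0% (0.6) and 88.6% vs 93.8% (0.7).

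**3. Does a repeated-measures model avoid the loss?** The generalised least squares variance was computed for two and for three timepoints, with complete data and exchangeable correlation.
- Free baseline means in each arm: SE 0.655 at r = 0.5 and 0.508 at r = 0.7, the same as the change score.
- Baseline means constrained equal: 0.567 and 0.468, the same as the adjusted analysis.

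Adding the midpoint changes neither. Time as a covariate does not by itself recover the precision; the constraint does.

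**4. Chance imbalance.** If the arms differ at baseline by d, the change estimate shifts by −(1 − r)d on average. Under the plan's inputs one SE of the baseline difference is 0.655 points. The shift is then 0.655 × 0.5 = 0.33 points at r = 0.5 and 0.655 × 0.3 = 0.20 at r = 0.7. Over repeated randomizations it averages to zero, which is why this is lost precision and not inflated type I error.

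**The case against.** **The model may not be a change score.** Section {20a} names the scales as the response and the change as the reported parameter, and {20c} makes time a covariate. Baseline may therefore enter as a repeated response, and would then not belong in a list of patient characteristics. This stands: a reader might infer that a change-score model is specified, and the article does not establish that. But step 3 shows that a repeated-measures model with free baseline means has the same standard error, so the point does not depend on which of the two is meant.

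**The constraint may be in a document not shown.** It may, and the word include in the covariate sentence leaves room for more items. If the constraint is already planned, nothing is lost. But the article does not merely leave adjustment to another document. It lists the covariates, and the list can be reviewed as it stands.

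**The size depends on r.** This stands. The large power contrast belongs to r = 0.5; from 0.7 upward the gain at 2.5 points is about 1 point or less. With 75 patients per practice and ICC 0.03, the r that matters weights the practice-level correlation by 2.25/3.22 = 0.70 and the patient-level one by 0.97/3.22 = 0.30, so stable practice means shrink the gain.

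A single patient-level covariate gives the full gain only when the two correlations are similar. With slope b its factor is 1 − 2br + b². Take a patient-level correlation of 0.5 as the slope. A practice-level correlation of 0.8 gives r = 0.71 and 1 − 0.71 + 0.25 = 0.54, against 0.58 for change. A practice-level correlation of 0.95 gives r = 0.814 and 0.44, against 0.37, so change would then be the better of the two unless the practice mean is also adjusted for.

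**Adjustment is not a cure-all.** Baseline is surveyed up to 12 months after randomization in unblinded practices. If recruitment differs systematically by arm, or baseline already carries some toolkit effect, adjustment does not remove the problem, and the constraint is then the less safe version. The change score has a related weakness.

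**Conclusion.** The point holds in a conditional form. As written, the covariate list leaves out the domain's baseline score, and under either reading of the model the treatment estimate is less precise than a baseline-adjusted one, unless baseline means are constrained equal. The variance could be 25% lower at r = 0.5 and 10% lower at r = 0.8. This rests on an assumed r, a common ICC, and similar correlations at patient and practice level.

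Three stronger readings are not supported.
- That every primary interval is certainly too wide: this depends on a constraint on which the article is silent.
- That the choice leaves the trial underpowered: the sample size used the single-score SD, a change score matches that variance at r = 0.5 and improves on it above.
- That the result is biased or the type I error inflated: no such effect follows from chance imbalance.

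It is a modest matter of efficiency, worth correcting because it costs so little.

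**What to change.** - In {20a}, add the baseline score of the same domain as a covariate in each of the eight primary models, and the matching baseline measure in the secondary patient-outcome models. If practice means may be much more stable than individual scores, add the practice mean of the baseline score as well.
- A longitudinal model with equal baseline means across arms is the alternative. The covariate version is safer here, because baseline is surveyed after randomization in unblinded practices.
- Make {20a}, {20c} and Trial status agree on the response, on how baseline enters, and on whether patients without a follow-up survey contribute.
- Report the unadjusted change as a sensitivity analysis.

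The cost is analysis wording and a variable already collected. Data processing was still under way according to Trial status; the change should be fixed before results by arm are seen. Asking for a baseline taken before toolkit start would not be practical, since data collection has ended.

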### Study patient participants

Patients are eligible to participate if they:
Are at least 18 years old,Are an active patient of a participating study practice as evidenced by at least two visits in a period of 24 months for any purpose, including at least one in the most recent 6 months,Are willing to complete three surveys over 2 years, andHave both an eligible chronic medical condition and an eligible chronic behavioral health condition, or at least three eligible chronic medical conditions. Eligible chronic medical conditions include arthritis; obstructive lung disease including emphysema, chronic bronchitis, or asthma; non-gestational diabetes; and heart disease manifested as heart failure or hypertension. Eligible behavioral health conditions include mood disorder (anxiety or depression), chronic pain (including headache, migraine, neuralgia, fibromyalgia, or chronic musculoskeletal pain), insomnia, irritable bowel syndrome, and substance misuse (substance use disorder, tobacco use, or problem drinking).

To determine patient eligibility, medical records are reviewed for a period of 24 months with the most recent date being within 12 months of the study start at each practice. Within this period, evidence of age, minimum number of visits, and medical and behavioral health conditions will be determined.

Evidence of medical conditions may take the form of a specific diagnosis on a problem list. Evidence of diabetes may also be indicated by 3 months of insulin or other diabetes medications (excepting metformin which is not specific to diabetes) or any hemoglobin A1C value greater than 6.4%. Evidence of heart disease may also be indicated by 3 months of cardiac medications specific to hypertension or heart failure (excepting beta-blockers and other medications with broader indications), or 3 sequential blood pressure measurements with mean systolic pressure > 140 mmHg or mean diastolic pressure > 95 mmHg.

Evidence of a behavioral health condition may take the form of a specific diagnosis on a patient’s problem list, 3 months of certain medications used for behavioral conditions (antidepressants, anxiolytics, opioids, antineuropathic agents, agents for alcohol use disorder or smoking cessation, etc.), or persistent failure to attain physiologic control of a medical problem evidenced as systolic blood pressure > 165 mmHg for 3 months or more or A1C > 9% for 6 months or more.

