#### Who will take informed consent? {26a}

Eligible patient participants are identified by review of EMRs in each participating primary care practice [28]. Acting as trusted third party, the DARTNet Institute [29] reviews the EMR data, identifies potential patient participants, and offers participation.

Eligible patients are mailed a letter describing the purpose of the study and that, if they choose to participate, they are requested to complete a brief set of surveys at three timepoints via web, paper, or phone. The letter also describes the process to opt-out as well as provides a phone number to call for more information on the study. The DARTNet Institute follows-up the letters with phone calls to eligible patients. Consent is administered and documented by phone, paper, or via web at the completion of the baseline set of surveys. Participating patients provide consent to link their EMRs to survey data and may discontinue participation at any time. All study materials are available in both Spanish and English.

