### Methods for additional analyses (e.g., subgroup analyses) {20b}

#### Subgroup analyses

Subgroup analyses will be conducted to understand if the IBH-PC toolkit is more or less effective for various patient and practice groups. Specific patient subgroups to be tested include gender, age in quartiles, race (white vs. other), education (less than high school graduation, high school diploma, college degree), degree of multi-morbidity (2 vs. > 2 qualifying conditions), and each of the qualifying conditions.

Specific practice subgroups will be analyzed based on practice size, staffing, geography, and financial structure.

These subgroup analyses will follow the same plan as the primary analysis except that an additional characteristic (representing subgroup membership) will be included as well as its interaction with the experimental condition.

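### The primary PROMIS-29 models list only sociodemographic covariates and leave out the qualifying conditions, which the trial already holds; this costs precision and leaves a limited opening for bias in change and in loss to follow-up

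*Protocol article*

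**What the plan says.** In the protocol article, Statistical methods for primary and secondary outcomes {20a}, each PROMIS-29 domain is modeled "as a function of experimental condition (active vs. control) and patient characteristics, with patients clustered within practices". The covariates are then named: "Patient characteristics will be measured at baseline and will include age, gender, race, ethnicity, marital status, employment, education, and income". The parameter of interest is the "adjusted change in PROMIS-29 domain from baseline to follow-up".

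Under Study patient participants, a patient enters with "both an eligible chronic medical condition and an eligible chronic behavioral health condition, or at least three eligible chronic medical conditions". There are four medical groups (arthritis, obstructive lung disease, diabetes, heart disease) and five behavioral groups (mood disorder, chronic pain, insomnia, irritable bowel syndrome, substance misuse). Under Subgroup analyses the conditions return as "degree of multi-morbidity (2 vs. > 2 qualifying conditions), and each of the qualifying conditions". Each subgroup variable is described there as a characteristic added to the primary plan.

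On timing, section {18a} says: "The baseline period reflects the first 0–12 months of participation after randomization". Section {26a} says: "Consent is administered and documented by phone, paper, or via web at the completion of the baseline set of surveys". On incomplete follow-up, section {20c} relies on the mixed model, "so subjects without complete data still contribute to the analysis".

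**The concern.** The conditions define this population and plausibly predict how pain, mood, sleep and fatigue develop over the 18 to 21 months between baseline and follow-up. The trial holds them for every enrolled patient, yet the stated primary model does not use them. Three things are at stake.

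- **Precision.** Variation in change that the conditions explain stays in the error term.
- **Comparability of enrolled patients.** Practices are randomized, but patients complete baseline and consent afterwards, with the practice's arm open. Randomizing practices does not by itself guarantee that the patients who agree are alike in the two arms.
- **Missing follow-up.** A likelihood-based mixed model handles missing outcomes validly only given what is in the model. If a condition drives both non-response and change, leaving it out weakens that assumption.

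**Working it through.** **Inputs from the protocol article.** SD 10, within-practice correlation 0.03, 40 practices of 75 patients, a 2.5-point difference, alpha 0.05/8 = 0.00625 and 90% power (Sample size {14}); 20 and 22 practices and 3006 baseline patients (Trial status). The article gives no condition prevalence by arm and no condition-specific change, so these are assumptions below.

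**1. The plan's own figure.** Design effect = 1 + 74 × 0.03 = 3.22. Standard error (SE) = 10 × √(2 × 3.22/1500) = 0.655. 2.5/0.655 = 3.815. With one-sided alpha 0.00625 (critical value 2.498), power is 90.6%, which matches the stated 90%. With two-sided alpha (2.734) it is 86.0%. Sidedness is not stated, and nothing below depends on it. With the achieved numbers, 3006/42 = 71.6 patients per practice, and SE = √[100 × (0.03 + 0.97/71.6) × (1/20 + 1/22)] = 0.645.

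**2. What can bias a change contrast.** Let a condition shift the score level by L and the change by g, and let its prevalence differ by d between arms.

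- Follow-up score alone: bias = d × (L + g).
- Change from baseline: bias = d × (L + g) − d × L = d × g. The level shift cancels.

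For d = 0.10 and g = 1, 2 or 3 points, the bias is 0.1, 0.2 or 0.3 points, which is 4%, 8% or 12% of the 2.5-point target. Over d = 0.05 to 0.20 and g = 1 to 5, it runs from 0.05 to 1.0 points.

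A simulation with assumed values (prevalence 60% vs 50%, L = 5, no true effect, 20 practices of 75 per arm, 600 runs) agrees within simulation error:

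| g | Follow-up only | Change | Change, condition added |
|---|---|---|---|
| 0 | 0.47 | −0.02 | −0.02 |
| 1 | 0.64 | 0.11 | 0.01 |
| 2 | 0.65 | 0.16 | −0.04 |
| 3 | 0.79 | 0.29 | −0.01 |

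If the analysis were a follow-up score adjusted only for the baseline score, the same simulation leaves 0.20 points even at g = 0, because adjusting for a noisy baseline score removes only part of the level difference.

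**3. Precision.** If the conditions explain a fraction Rb of between-practice and Rw of within-practice variance, the variance of the effect falls by 1 − [0.03(1 − Rb) + 0.97(1 − Rw)/71.6] / [0.03 + 0.97/71.6].

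- Rb = 0, Rw = 1%: 0.3%.
- Rb = 10%, Rw = 3%: 7.8%.
- Rb = 20%, Rw = 5%: 15.3%.

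This borrows the article's correlation for the scores; the correlation for change is not given.

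**4. How the covariate enters.** In a longitudinal model with arm, time and arm-by-time, a condition main effect adds the same amount at baseline and follow-up. It therefore drops out of the arm-by-time term when data are complete. Only a condition-by-time term, or a condition covariate in a model for change or for baseline-adjusted follow-up, adjusts the contrast.

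**The case against.** The case against acting has several sound parts.

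**The safeguards are real.** A third party identifies patients from medical records and invites them ({26a}). They come from a random panel of the practice's active adults ({15}). Practices are not told who is eligible or enrolled ({15}, {17a}). Systematic differential enrollment by condition is therefore unlikely, though these steps do not control who agrees or who responds at follow-up.

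**A reader might infer that case-mix differences between arms pass straight into the estimated effect.** The documents do not support that. The target is change, so level differences cancel, and no imbalance is reported.

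**A reader might also infer an inflated false-positive rate.** The arithmetic can be done: a fixed bias of 0.3 points at SE 0.655 moves the two-sided per-domain rate from 0.00625 to 0.012. That treats the imbalance as systematic. Chance imbalance between randomized practices is already in the cluster-level standard error and inflates nothing.

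**The list may not be exhaustive.** Its wording leaves room for more covariates, and the analysis plan is not shown. Omitting conditions is also a legitimate choice in a randomized trial. But the article does name a list, and its subgroup section treats subgroup membership as an addition. Age, gender, race and education are also subgroups and already covariates, so that inference is strong but not conclusive. The named list can be improved from data in hand.

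**Simple condition indicators are not enough.** Sustained high blood pressure or A1C counts as behavioral evidence under the eligibility criteria but belongs to none of the five named groups. Medication evidence does not always point to one group.

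**Conclusion.** The point holds in a limited form. The stated primary covariates are purely sociodemographic and omit the qualifying conditions, which the trial already extracts. The consequence is some lost precision and a limited opening for bias through condition-related change or loss to follow-up. It is not a demonstrated bias.

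The size cannot be computed from the documents. Under the assumed explained variances, the variance reduction is about 0.3% to 15%, so the gain may be negligible. Any bias equals the prevalence imbalance times the difference in change: 0.1 to 0.3 points for a 10-point imbalance and a 1 to 3 point difference. It would be bias only if the imbalance were systematic, through recruitment or follow-up. This is a low-cost improvement to a prespecified list, not a defect that invalidates the analysis.

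**What to change.** In section {20a}, add to the prespecified patient characteristics:

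- an indicator for each qualifying medical and behavioral condition group, with a separate indicator for patients who qualify only through the medication evidence or the uncontrolled blood pressure or A1C evidence; or, at the least,
- the number of qualifying conditions and the entry route.

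Derive them from the extract used for eligibility, not from later records that the toolkit's case identification could alter. A cut-off at randomization is not advised without checking, because the eligibility window is tied to study start.

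Enter them so that they adjust the change: condition-by-time terms in the longitudinal model, or covariates in a baseline-adjusted follow-up model. Keep the sociodemographic-only model as a sensitivity analysis.

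Cost: a few degrees of freedom on 3006 baseline patients, and some work to map medication and physiologic evidence to groups. Coding error in the medical records means the adjustment will be partial.
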